#### Clinical endpoints

The effects of CAD screening (versus no CAD screening) in terms of major adverse cardiac events (the first occurrence of any component of the composite outcome, which comprise acute coronary syndrome, coronary revascularization, hospitalization for heart failure or all-cause death); major cerebrovascular events (the first occurrence either of stroke, hospitalization for TIA, or carotid revascularization); major adverse limb events (the first occurrence of any component of the composite outcome, comprising PAD, ischemic diabetic foot, lower-limb revascularization (angioplasty or surgery) or amputation); and CKD or end-stage kidney disease (ESKD, defined as requirement of any sustained renal replacement therapy or kidney transplantation). Each component of these composite endpoints will also be considered individually. Major cerebrovascular events, major adverse limb events and ESKD will be considered during follow-up among participants without a history of each appropriate condition at baseline. Clinical endpoints will be determined according to ICD-10 and codes of the French classification of medical procedure (CCAM) as presented in Additional file 2: Table S2.

Finally, SCADIAB study will also assess the frequency of routine CAD screening, expressed as the number of examinations performed per individual per year.

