A routine CAD screening induces high healthcare expenses as it leads to invasive investigations, endovascular and surgical revascularizations as well as intensification of pharmacological therapies. To the best of our knowledge, the cost-effectiveness of routine CAD screening has not been evaluated prospectively in population with T2DM and a very high cardiovascular risk. Only two economic studies, based on Markov models, have addressed this question by comparing different strategies in Japanese and American populations: no screening, screening (with stress echocardiography, myocardial scintigraphy coupled with stress test, or stress electrocardiogram) [21, 22]. Their results were very limited by model’s hypothesis; uncertainty surrounding epidemiological and utilities data used; and costs of care, which may differ greatly across countries. In this context of discrepancy between lack of evidence and current guidelines and clinical practice, we aim to estimate the effectiveness and cost-effectiveness of systematic CAD screening in patients with T2DM and a very high cardiovascular risk.

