### Study population

#### Inclusion criteria

Eligible participants must meet all of the following criteria:Age = 40 years or older,Affiliation to the general health insurance scheme in France,Diagnosis of T2DM,Duration of T2DM ≥ 7 years,Two or more additional cardiovascular risk factors (obesity, hypertension, hypercholesterolemia, or tobacco smoking using the chronic obstructive pulmonary disease (COPD) as a proxy),At least one microvascular or macrovascular disease: carotid stenosis, transient ischemic attack (TIA), stroke, lower-limb peripheral artery disease (PAD), CKD, severe diabetic retinopathy with requirement of laser photocoagulation, or peripheral or autonomic diabetic neuropathy.

Diagnosis will be determined based on the list of 100% health insurance coverage for chronic diseases in France (including T2DM, hypertension, TIA, stroke, PAD, CKD, COPD), the history of diseases of interest or surgery (coronary, carotid or lower-limb revascularization, bariatric surgery, kidney transplantation) according to the International Classification of Diseases Code Tenth Revision (ICD-10) (Additional file 1: Table S1), or at least 3 deliveries of one or more corresponding drugs as appropriate (antidiabetic, anti-obesity, antihypertensive or lipid-lowering drugs) over one year.

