#### Exclusion criteria

One of the following:The presence of CAD (defined as a history of acute coronary syndrome, coronary revascularization, angina pectoris, or unstable angina).Any visit to an emergency department for chest pain resulting for admission to a cardiac intensive care unit.

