### Cost-effectiveness of routine CAD screening in patients with diabetes

Systematic CAD screening strategy leads to more invasive examination, especially coronary angiography, which is associated with increased risk of complications [11, 12]. Routine CAD screening encourages also revascularizations and intensification of pharmacological treatments, despite uncertainties in terms of related benefits. In the FACTOR-64 study, CAD screening was not associated with a significant reduction in major cardiovascular events despite intensive pharmacological control of cardiovascular risk factors (and some coronary revascularizations) in patients with a positive screening test, while individuals assigned to control group and those with a negative screening test had only conventional cardiovascular treatment goals [13]. Furthermore, BARDOT (Basel Asymptomatic high-Risk Diabetics' Outcome Trial) study showed that combined medical therapy and invasive strategy (coronary angiography followed or not by revascularization) for silent CAD, compared with medical treatment alone, was associated with reduced scintigraphic CAD progression, but no significant difference was observed in terms of hard clinical events in high risk T2DM patients [28]. Therefore, to avoid unjustified health expenses and misuse of collective resources associated with routine CAD screening, we conduct the SCADIAB study to assess the cost-effectiveness of this strategy in people with T2DM and a very high cardiovascular risk.

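### The no-history rule omits CKD, so CKD present at inclusion can count as a renal event; MACE also counts revascularization that screening itself can lead to

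*Protocol article*

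**What the plan says.** **Renal endpoint.** The Clinical endpoints section defines the renal outcome as CKD or ESKD, where ESKD means sustained renal replacement therapy or transplantation. The same section limits some endpoints to people free of the condition: "Major cerebrovascular events, major adverse limb events and ESKD will be considered during follow-up among participants without a history of each appropriate condition at baseline". CKD is not in that list. The Inclusion criteria require "At least one microvascular or macrovascular disease: carotid stenosis, transient ischemic attack (TIA), stroke, lower-limb peripheral artery disease (PAD), CKD" or one of a few further conditions, so CKD alone can satisfy this criterion.

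**Cardiac composite.** MACE is the first of "acute coronary syndrome, coronary revascularization, hospitalization for heart failure or all-cause death". Events are identified by ICD-10 and procedure codes. The text does not limit revascularization to urgent, symptom-driven or ACS-related procedures. The Background says of routine screening that "it leads to invasive investigations, endovascular and surgical revascularizations", and the Discussion says: "Routine CAD screening encourages also revascularizations and intensification of pharmacological treatments, despite uncertainties in terms of related benefits".

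**Use of the counts.** The Economic endpoints section links 5-year costs to the total of major cardiovascular and renal events. The Statistical analysis plan section mentions only major cardiovascular events for the same analysis. Each component of the composites is also to be analysed singly.

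**The concern.** The protocol chose to state which endpoints need a clean baseline. Stroke, TIA and PAD are qualifying conditions, and the endpoints they belong to are restricted. CKD is also a qualifying condition and part of an endpoint, but its endpoint is restricted only for ESKD. An analyst who follows the sentence literally would keep patients with CKD at baseline in the risk set for CKD. Their first CKD code after 1 January 2015 would then be an event, although nothing new has happened. Such events occur in both groups whatever screening does, so they pull a ratio towards 1 and swell the totals set against cost.

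The cardiac composite raises a related but smaller difficulty. A planned procedure after a positive test is a consequence of the strategy under study. When it is the first event, it scores the same as death and hides any later ACS or heart-failure admission in that composite. The composite then mixes what the strategy does with what it achieves.

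**Working it through.** **Plan's own figure.** The article gives no number for either endpoint. Its only size figure is the eligible population in Sample size estimation: 2,400,000 × 0.38 × 0.10 = 91,200, which agrees with the stated minimum of 90,000. The point does not depend on it.

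**CKD, on the text.**
- Is CKD a qualifying condition? Yes (Inclusion criteria).
- Is CKD a component of the renal endpoint? Yes (Clinical endpoints).
- Does the no-history rule name CKD? No; it names cerebrovascular events, limb events and ESKD.
- Does any other sentence in the article keep baseline CKD out of the count? None does.

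**CKD, illustrated size.** Let *p* be the share with CKD at baseline and *i* the 5-year risk of new CKD in the rest. Assume that every baseline case is coded again in follow-up. None of these values is in the documents.

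Share of counted CKD events that are prevalent = *p* / (*p* + (1 − *p*)*i*)

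- *p* = 0.20, *i* = 0.15: 0.20 / (0.20 + 0.12) = 0.625, or 63%
- *p* = 0.40, *i* = 0.10: 0.40 / (0.40 + 0.06) = 87%
- *p* = 0.60, *i* = 0.05: 0.60 / (0.60 + 0.02) = 97%

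Dilution, with *i* = 0.10, a true risk ratio of 0.80 for new CKD and equal *p* in both groups: observed RR = (*p* + (1 − *p*) × 0.10 × 0.80) / (*p* + (1 − *p*) × 0.10)

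- *p* = 0.20: 0.264 / 0.280 = 0.94
- *p* = 0.60: 0.632 / 0.640 = 0.99

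If fewer baseline cases are coded again, the prevalent share and the dilution shrink. With CKD in the no-history rule, the prevalent share is 0%, apart from misclassified baseline status.

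**MACE, on the timeline.** Groups are fixed by tests before the index date of 1 January 2015. The exclusion of CAD, defined as a "history of acute coronary syndrome, coronary revascularization, angina pectoris, or unstable angina", should remove patients revascularized before that date. Two routes remain by which a test can lead to a procedure within follow-up:
- a test late in 2014;
- a repeat test in 2015–2019. The Background survey reports screening once a year (42%), every two years (20%) and every three years (33%), and the Statistical analysis plan section defines a subgroup tested only once during follow-up.

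The no-screening group is defined over the selection period only, so its members may also be tested, and revascularized, after the index date.

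**MACE, illustrated size.** Assume constant, independent hazards and no effect of screening on the other components. Let *r* be the yearly rate of the other components, *c* the yearly revascularization rate in controls, and *k* the ratio of revascularization rates, screened to control. Composite HR = (*r* + *kc*) / (*r* + *c*). All values are assumed.

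- *r* = 6%, *c* = 0.5%, *k* = 1.25: 6.625 / 6.5 = 1.02
- *r* = 4%, *c* = 1%, *k* = 1.25: 5.25 / 5 = 1.05
- *r* = 2%, *c* = 1%, *k* = 2: 4 / 3 = 1.33
- *r* = 4%, *c* = 1%, *k* = 0.8 (the reciprocal of 1.25): 4.8 / 5 = 0.96

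The last line shows that the sign depends wholly on *k*, which the documents do not give. Small distortions would matter at this sample size. With 90,000 patients split 50:50, two-sided 5% and Schoenfeld's formula, HR 1.02 (25,175 events) reaches significance with probability 33%, and HR 1.05 (20,343 events) with probability 94%. Leaving revascularization out gives HR 1.00 in every line, by the assumption of no other effect.

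**The case against.** **On CKD.** The reference to ESKD may be shorthand for the whole renal endpoint, since the same sentence restricts the other endpoints that overlap with the inclusion conditions. Additional file 2 (Table S2), which is not shown, may define incident or worsening CKD. Both are possible. But the article describes that table as the source of the codes, while the population restriction is set in the main text, and there CKD is missing. A reader might infer that the renal endpoint will in fact be mostly prevalent disease. The documents do not support that as a fact: they give neither the prevalence of CKD nor how often it is coded again.

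**On MACE.** A reader might infer that the composite is biased against screening. The documents do not establish this. Exposure precedes follow-up, earlier revascularization is an exclusion, and controls may be tested later. Removing screened patients who have already been revascularized could even lower the later rate in the screened group. Nor is revascularization a non-outcome: it is a real clinical event, and procedures for new symptoms are legitimate endpoints. Comparability with the trials in Table 1 adds little. None of the five lists revascularization in its primary outcome, but those outcomes differ among themselves and an amended composite would match none of them.

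**On mitigation.** Analysing components singly makes revascularization, death, ACS and heart failure each visible, and it leaves ESKD clean. It does not correct the composite, the CKD component or the event totals.

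**Conclusion.** The CKD gap holds on the text. Applied as written, the rule lets CKD present at inclusion count as a follow-up event. Under the assumed ranges (baseline CKD 20–60%, new CKD 5–15%, every baseline case coded again), 63–97% of counted CKD events would be prevalent, and a true RR of 0.80 would appear as 0.94–0.99 when new CKD is 10%. The true size is unknown. Renal counts enter the cost-consequence analysis according to the Economic endpoints section; the Statistical analysis plan section omits them, so the two descriptions should be aligned.

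The MACE point is real but lesser. The composite can absorb procedures that the protocol itself attributes to screening, through tests late in 2014 and repeat tests in follow-up. The direction and size of the effect are not fixed by the documents.

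Both concern secondary endpoints. The primary endpoint, incremental cost per life year saved, does not use these event counts.

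**What to change.** 1. Add CKD to the no-history rule. Assess new CKD only in participants without CKD at baseline, and ESKD in all participants without ESKD at baseline. Because the two risk sets differ, report them separately. The cost is a few words and a smaller denominator for new CKD.

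2. Keep the current MACE, but prespecify beside it a composite of ACS, heart-failure hospitalization or all-cause death, and base conclusions about clinical benefit or harm on that one. Report revascularization separately, as a component and as resource use. This needs no extra data, since every component is already to be analysed. The cost is fewer events in the new composite and the loss from it of procedures done for new stable symptoms, which stay visible in the separate report.

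Both changes should be fixed before the outcome data are analysed.

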### Strengths and limitations

The key strength of our study is the collection of a comprehensive range of clinical features, cardiovascular procedures, history of pharmacological therapies or surgery, major events and survival status in the whole French population of patients with T2DM and a very high cardiovascular risk during an overall period of 12 years. SCADIAB findings will have a broader generalizability for all T2DM patients at a very high cardiovascular risk. Our study will provide a line of complementary evidence (further to RCTs’ findings) in terms of routine CAD screening in a contemporary cohort of patients with T2DM in real-world settings. SCADIAB will be more economical and time efficient than RCT, but a number of intrinsic limitations need to be acknowledged. The retrospective and non-randomized design of our study is subject to bias (selection, information, detection) and confounding factors. To limit selection bias, our study population will be rigorously defined using pre-specified inclusion criteria (T2DM for at least 7 years, with at least 2 cardiovascular risk factors and one or more organ damage) extracted from reliable and valid SNDS database. The 7-year selection period leading to assignment of each individual to one of the two study arms (CAD screening or absence of CAD screening) will limit information bias. We will use validated algorithms to identify inclusion criteria and endpoints [29–31]. Also, the cardiovascular investigation required for study arms assignment (stress test, scintigraphy, stress echocardiography…) will be recorded exhaustively in the SNDS database. We believe that the detection bias will be limited in our study as we have access to the SNDS database covering the whole French population including death registry. Finally, we will use the hdPS method to control measurable confounding factors as well as unknown or unmeasurable ones [32–34].

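### A first PAD diagnosis with no qualifier counts as a major limb event, so this secondary composite is open to differential detection, which full database coverage does not remove

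*Protocol article*

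**What the plan says.** All references are to the Protocol article.

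- **Clinical endpoints** defines "major adverse limb events (the first occurrence of any component of the composite outcome, comprising PAD, ischemic diabetic foot", and completes the list with "lower-limb revascularization (angioplasty or surgery) or amputation". The Abstract gives the same four components among the main secondary endpoints.
- The same section defines the cerebrovascular composite as "the first occurrence either of stroke, hospitalization for TIA, or carotid revascularization". The cardiac composite likewise counts heart failure only when it leads to hospitalization. PAD has no such condition.
- The limb endpoint "will be considered during follow-up among participants without a history of each appropriate condition at baseline".
- The section adds: "Each component of these composite endpoints will also be considered individually". The operational codes are in Additional file 2, Table S2, which is not shown.
- **Screening group** requires at least one cardiac test during the selection period. **Recruitment of participants and follow-up** states that the propensity-score variables are measured in that same period, before 1 January 2015.
- **Strengths and limitations** lists detection among the biases of the design, then says: "We believe that the detection bias will be limited in our study as we have access to the SNDS database", pointing to national coverage and the death registry.

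**The concern.** Revascularization and amputation are procedures. A PAD diagnosis is a label that enters a claims database only if someone looked for the disease and coded it. Because people with a history of the condition are left out, a PAD event here is a first coded PAD. It ranks equally with an amputation and is the event counted if it comes first.

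The groups are formed by usual-care cardiac testing, not by randomisation. Patients referred for such tests may plausibly be examined more for arterial disease elsewhere. Two mechanisms then pull in opposite directions:

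- More examination of screened patients after the index date produces more coded PAD, and screening appears harmful to the limb.
- More examination of screened patients before the index date removes those found to have PAD from the population at risk, and screening appears protective.

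At stake is the interpretation of one of the main secondary endpoints. With a cohort this large, a modest difference in detection could be reported as a statistically significant effect of screening.

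**Working it through.** **The plan's own figure.** The only size given is the number eligible (Sample size estimation): 2,400,000 free of CAD × 0.38 with two or more risk factors × 0.10 with vascular disease = 91,200. This agrees with the stated minimum of 90,000. No limb-event rate, PAD share, PAD testing rate or allocation is given.

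**Spurious hazard ratio.** Let *f* be the share of first limb events in the no-screening group that are PAD diagnoses, and *d* the ratio (screened to unscreened) of PAD detection. If screening has no true effect and the other components are unaffected, then approximately

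HR = (1 − *f*) + *f* × *d*.

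Both inputs are assumptions. For *f* = 0.4 and *d* = 1.25: 0.6 + 0.4 × 1.25 = 1.10. Over a range:

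| *f* | *d* = 1.1 | *d* = 1.25 | *d* = 1.5 |
|---|---|---|---|
| 0.2 | 1.02 | 1.05 | 1.10 |
| 0.4 | 1.04 | 1.10 | 1.20 |
| 0.6 | 1.06 | 1.15 | 1.30 |
| 0.8 | 1.08 | 1.20 | 1.40 |

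In the other direction, *f* = 0.4 and *d* = 0.8 give 0.6 + 0.4 × 0.8 = 0.92. With PAD out of the composite, *f* = 0 and this component contributes nothing (HR 1.00).

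**Chance that a spurious ratio is significant.** The article sets α at 5%; I take it as two-sided. With *D* events and a fraction *a* screened, power = Φ(|ln HR| × √(*D* × *a* × (1 − *a*)) − 1.96). Assume 45,000 at risk and a 5-year incidence of 10%, so *D* = 4,500.

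- HR 1.10, *a* = 0.3: 0.0953 × √945 − 1.96 = 0.97, power 0.83.
- HR 1.10, *a* = 0.5: 0.0953 × √1,125 − 1.96 = 1.24, power 0.89.
- HR 1.02, same *D*: 0.09 to 0.10.
- HR 1.20, same *D*: about 1.00.

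With half the events (2,250), HR 1.10 is significant with probability 0.55 to 0.62. With twice as many (9,000), it is 0.99 or more.

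**Does adjustment or coverage remove it?** The score is built from pre-index variables. It may partly balance earlier intensity of care, but it cannot equalise examinations made in 2015–2019. Coverage means that what is coded is captured for nearly everyone. It does not mean that undiagnosed PAD is as likely to be found in one group as in the other.

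**The case against.** The strongest replies are these.

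- **Components are analysed alone.** This is planned, and it stands. A reader might infer that the first-event rule hides the effect on revascularization and amputation. It does not, because both will be seen separately. What remains is that the composite itself is affected.
- **No figure shows that PAD dominates.** This stands. A reader might infer that the endpoint mostly measures who is examined, or is little more than time to a first PAD code. The article gives neither a PAD share nor testing rates by group, so that reading is unsupported. The low corner of the table (1.02) is as compatible with the text as the high corner (1.40).
- **Table S2 is unseen.** It may restrict PAD to hospital-coded or severe disease. That would lessen the problem without removing it.
- **Closer vascular follow-up is an inference.** This stands. The design requires one cardiac test and prescribes no follow-up of the leg arteries. Differential work-up is plausible, not built in.
- **The coverage remark is hedged and partly right.** Detection bias is openly listed, and coverage does support completeness of recorded events and deaths. To call the remark simply wrong goes too far. The stated reason is insufficient for the conclusion drawn from it.
- **The procedural components are not immune.** Revascularization can follow from finding PAD, so the remedy is partial.

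**Conclusion.** The point holds as a vulnerability, not as a demonstrated bias. A first PAD diagnosis, unqualified in the text shown, sits in a composite of major limb events, while comparable components of the other composites require hospitalization. Neither the pre-index propensity score nor national coverage secures equal PAD work-up after the index date.

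The size and net direction are unknown from the article. The illustrative hazard ratio of about 1.10 rests on an assumed 40% PAD share, a 1.25-fold detection ratio and no effect on the other components. Its 0.83 to 0.89 chance of significance further assumes 4,500 events and 30% to 50% screened. The calculation does show that PAD need not be the majority of events for the bias to matter.

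The consequence is confined to a secondary endpoint and its interpretation. The effect side of the primary endpoint is life years, which PAD coding does not change.

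**What to change.** 1. In Clinical endpoints and the Abstract, take PAD diagnosis out of the limb composite. Alternatively, count PAD only when it leads to hospitalization, as is done for TIA.
2. Report new PAD as a separate outcome, labelled detection-sensitive. The planned component analyses already provide most of this.
3. Rest limb conclusions on revascularization and amputation, noting that revascularization may itself depend partly on work-up. If feasible, report vascular testing during follow-up by group.
4. In Strengths and limitations, limit the coverage statement to completeness of recorded events and deaths, and say that coverage does not ensure an equal chance of diagnosis.

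The change is one of definition and wording. According to Study progress, access to the database was still being arranged, so it can be made before extraction. The cost is fewer events, and hence less precision, in one secondary composite.

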### Recruitment of participants and follow‑up

The data will be extracted from January 1, 2008 to December 31, 2019. A selection period will be defined by the 7 years (January 1, 2008 to December 31, 2014) preceding the index date. It will enable us to identify eligible patients and measure all the variables needed for the calculation of the high dimension propensity score (hdPS). Each participant will be assigned to one of the two study groups on the index date (January 1, 2015), and then followed up to December 31, 2019 (Fig. 1).

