### Study groups and methods of CAD screening

#### Screening group

Individuals who had at least one screening exam (stress electrocardiogram test, stress echocardiography, myocardial scintigraphy coupled with stress test or pharmacological stimulation using adenosine, or coronary CT scan) (Table 2) during the selection period (2008–2015).

**Table 2 Tab2:** Codes used to identify tests to screen coronary artery disease

Tests	Procedure codes
Stress test	DKRP004, EQRP002, EQRM001
Myocardial scintigraphy coupled with stress test or pharmacological stimulation using adenosine	DAQL001, DAQL010, DAQL011, DAQL009
Stress echocardiography	DAQM003, DZQM002, DBQM001
Coronary CT scan	ECQH010
Procedure codes: Codes of the French classification of medical procedure (CCAM)	

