#### No-screening group

Participants who never experienced a screening exam as described above during the selection period (2008–2015), except resting electrocardiogram.

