### Statistical analysis plan

The data will be analysed by the biostatistician of the “Clinical Epidemiology Unit” of the University Hospital of Bordeaux (USMR). Analyses will be performed using SAS® software, version 9.4 or later (SAS Institute, Cary, NC, USA, http://www.sas.com) and all tests will be performed at the first-order error risk α = 5%. The flow-chart (CONSORT), as well as the characteristics of patients at inclusion (eligibility criteria, epidemiological, clinical, biological characteristics and treatment use) will be presented. Confounding factors will be taken into account through a hdPS score that will involve around 500 variables, according to the Bross formula [26]. A principal component analysis will then allow us to reduce the dimensionality to 30 components, and the goodness of fit of this hdPS score will be estimated by a graphical comparison of the score distribution and by standardized mean differences between the two study groups [27]. Comparisons between the two groups will be carried out with and without adjustment for the hdPS score, and the hypotheses of the different regression models chosen, will be systematically verified.

Regarding the analysis of the primary endpoint, a gross estimate of the incremental cost per life-year gained at 5 years will be conducted. The confidence interval (CI) of this incremental cost-effectiveness ratio will be estimated by boostrap (5000 iterations). The analysis will be performed as Intent to Treat. To investigate a possible relationship between the frequency of screening and survival, we will define four different subgroups: screening conducted at least once a year, less than once a year (and at least once every two years), less than once every two years (and at least once every three years), and only once during the follow-up period.

A cost-consequence analysis will be performed linking results of all direct costs (observed during the following period) and results on major cardiovascular events. A budget impact analysis will be conducted to determine the public expenses of the spread of a systematic screening for silent ischemic CAD.

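### Screening frequency is counted from indication-free procedure codes with no end at incident CAD, so tests done after a coronary event count as screening; the size and sign of the resulting error are unknown

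*Protocol article*

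**What the plan says.** Clinical endpoints adds a practice measure: "the frequency of routine CAD screening, expressed as the number of examinations performed per individual per year". The unit is the individual's year, not the CAD-free year.

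Table 2, under Screening group, lists the "Codes used to identify tests to screen coronary artery disease". These are procedure codes for stress test, scintigraphy, stress echocardiography and coronary CT. No diagnosis or reason for the test is attached.

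The Statistical analysis plan section uses frequency a second time: "To investigate a possible relationship between the frequency of screening and survival, we will define four different subgroups". The upper bands are "screening conducted at least once a year, less than once a year (and at least once every two years", followed by a band down to one test every three years. The last band is "and only once during the follow-up period", which places the count after the index date of 1 January 2015. Participants are assigned on that date "and then followed up to December 31, 2019".

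CAD is handled at entry only. Exclusion criteria removes "The presence of CAD (defined as a history of acute coronary syndrome, coronary revascularization, angina pectoris, or unstable angina", as a history. During follow-up, acute coronary syndrome and coronary revascularization are components of the cardiac composite.

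**The concern.** Silent CAD can be screened for only while a patient has no known CAD. After an infarction, an angina diagnosis or a revascularization, the same procedure code records follow-up of known disease. Neither the codes nor the word routine separates the two, and no rule in the article ends the count at the first coronary event.

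Two outputs are exposed:

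- **The frequency endpoint.** It mixes screening with disease follow-up, so it no longer measures screening practice, which the Conclusions present as a study output.
- **The frequency–survival analysis.** A coronary event can raise both later testing and the risk of death. Frequent testing could then look harmful through reverse causation. Adjustment for a propensity score built on variables measured before the index date cannot remove this, because the event comes later.

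**Working it through.** The plan gives no figure for this point: no CAD incidence for this cohort and no testing rate before or after CAD. The check is therefore a sensitivity range on stated assumptions.

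**Inputs**

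- CAD incidence h: 2% and 3% a year (assumed; observed composite rates in Table 1 are 0.6–3% a year, for other populations and outcomes).
- Mortality: 5% a year before CAD and 8% after (assumed).
- Examinations after CAD, p: 0.4 and 0.6 a year (assumed).
- Examinations before CAD, s: 0.10, 0.20 and 0.33 a year (assumed), or a value taken from the physician survey in Background. There 69–80% screen routinely: 42% yearly, 20% every two years, 33% every three years. If that carried over to patients, 0.42×1 + 0.20×0.5 + 0.33×(1/3) = 0.63. Then 0.63×0.69 = 0.43 and 0.63×0.80 = 0.50 a year.

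**Step 1: error in the rate**

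Let T0 and T1 be mean CAD-free and post-CAD person-years over 5 years, and f = T1/(T0+T1). The all-examination rate is (s·T0 + p·T1)/(T0+T1). Its relative error against the CAD-free rate s is f × (p/s − 1).

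- h = 2%: T0 = (1 − e^(−0.07×5))/0.07 = 4.219, T1 = 0.196, f = 0.0443.
- h = 3%: T0 = (1 − e^(−0.08×5))/0.08 = 4.121, T1 = 0.289, f = 0.0654.

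| s (per year) | Smallest error | Largest error |
|---|---|---|
| 0.10–0.20 | 0.0443×(0.4/0.20 − 1) = +4.4% | 0.0654×(0.6/0.10 − 1) = +32.7% |
| 0.33 | 0.0443×(0.4/0.33 − 1) = +0.9% | 0.0654×(0.6/0.33 − 1) = +5.4% |
| 0.43–0.50 (survey) | 0.0654×(0.4/0.504 − 1) = −1.3% | 0.0654×(0.6/0.4347 − 1) = +2.5% |

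The sign turns negative once CAD-free patients are tested more often than patients with CAD. At h = 1% (f = 0.0225) and s = 0.10–0.20 the error is about 2–11%.

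**Step 2: the at-least-yearly subgroup**

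The same model was simulated with 1,000,000 patients per scenario and Poisson examinations. At least yearly means 5 or more examinations among 5-year survivors. CAD patients are 9–13% of all survivors. Their share of the top subgroup is:

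| Testing before CAD | CAD share of top subgroup |
|---|---|
| 0.10–0.20 a year, same for all | 37–98% |
| 0.33 a year, same for all | 12–35% |
| Survey mix across patients | 5–12% |

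A simpler bound points the same way. With c the 5-year CAD risk, p1 and p0 the chances that a CAD and a CAD-free patient are classed as at least yearly, the share is c·p1/(c·p1 + (1−c)·p0). For assumed c = 3–24%, p1 = 20–60% and p0 = 2–42% it runs from 1.5% to 90%. With p0 = 29–34% (42% × 69–80%) it is 2–40%. It passes 50% only if p0 is below c·p1/(1−c), which is 0.6–19%.

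**Step 3: would the CAD-free rate also repair the subgroups?**

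No. A patient with one examination and CAD at 10 months scores 1/(10/12) = 1.2 a year and enters the top subgroup. At s = 0.10–0.20, regrouping survivors on examinations per CAD-free year leaves CAD patients at about 45–91% of that subgroup. At s = 0.20 and p = 0.4 it makes matters worse: 37% rises to 45% (h = 2%) and 48% to 56% (h = 3%). Stopping the count but keeping a 5-year denominator pushes the share below 5%, a distortion in the other direction.

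**The case against.** The strongest reply is that the article never says post-infarction tests will be counted. It speaks of routine screening and of silent disease, and an operational rule may sit in a full protocol or analysis plan that is not shown. The possibility of such a rule stands. But the article does more than stay silent: it fixes a unit, a code list, four bands and a follow-up window, and applied as written they score those tests as screening. The same section restricts several clinical endpoints to participants without the condition at baseline; screening frequency has no such restriction.

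A second reply is that the count might be meant for the selection period, where CAD is excluded. The problem would then largely disappear, but the wording of the last band points to follow-up.

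A third reply concerns size, and it stands. A reader might infer that the reported frequency must be overstated, or that the most frequently tested subgroup will consist mainly of patients with CAD. The documents support neither. Large figures arise only when CAD-free patients are rarely tested. With the survey mix, the rate error straddles zero and the top subgroup is not enriched (5–12% against 9–13% of survivors). The survey is physician self-report, so true patient rates may be lower.

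A reader might also infer that the main result is biased. It is not, on this ground: the control group is "Participants who never experienced a screening exam as described above during the selection period (2008–2015), except resting electrocardiogram", so allocation uses examinations before follow-up.

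**Conclusion.** The concern holds as a fault of definition. The endpoint named routine CAD screening also captures disease follow-up, because the codes carry no indication and the count has no end at incident CAD.

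Its numerical effect cannot be fixed from the documents. Under the assumed incidence, mortality and post-CAD testing, the rate error is about +4% to +33% at 0.10–0.20 examinations a year before CAD, 1–5% at 0.33, and about -1% to +2.5% with the survey mix. Enrichment of the at-least-yearly subgroup with CAD is possible but not established.

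The reach is one secondary practice measure and one exploratory frequency–survival analysis. The incremental cost per life-year and the between-group hazard ratios are untouched by this counting rule.

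**What to change.** **Clinical endpoints.** Define screening frequency as examinations per person-year free of CAD. End both the count and the person-time at the first acute coronary syndrome, angina or unstable angina code, coronary revascularization, death or 31 December 2019.

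**Statistical analysis plan, frequency subgroups.** Do not carry that individual rate over, for the reason shown in Step 3. Choose one of two routes:

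- Classify frequency from examinations before the index date, in the selection period already used for group assignment. This requires the CAD exclusion to run up to the index date, and the last band to be reworded for that window.
- Treat pre-CAD examination frequency as a time-updated exposure in the survival model.

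**Cost.** The endpoint change is one sentence and a date cut-off, using event dates that the clinical endpoints already need, and loses slightly under 5% to 7% of person-time in the scenarios above (f = 0.044–0.065). The subgroup change takes a little extra analysis work. Neither removes a symptom-driven test done shortly before the first CAD code; that should be named as a limitation.
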